#### Secondary outcome measures

##### Sociodemographic and clinical data

For each participant, sociodemographic information (age, sex, educational level, marital status, main activity) and clinical data (onset of schizophrenia, number of hospitalizations, dosage of antipsychotic medication, drug consumption such as tobacco, alcohol and cannabis, history of neurostimulation treatment) will be registered in the patient’s case report form (CRF). Note that the pharmacological treatment is recorded at baseline for each patient and any change will be recorded in the patient’s CRF by the psychiatrist in charge. The Edinburgh handedness inventory will be used to ensure that all patients are right-handed [32].

##### Clinical assessments

The Auditory Hallucinations Rating Scale (AHRS) is widely used to assess the presence and severity of AVH across seven items investigating frequency, level of reality, loudness, number of voices, length of the content, level of distraction, and distress [27]. The HCS is linked to the AHRS and evaluates the percentage of AVH change [33]. On a scale from 0 to 20, a default score of 10 will be attributed to a narrative description of the patient AVH prior to the rTMS sessions (baseline, W0). For the re-assessment of the AVH following rTMS treatment, scores will be evaluated again, and ascribed lower values (with 0 corresponding to total absence of AVH) if AVH severity decreases, whereas a higher score will be ascribed if AVH severity is worse (with 20 indicating twice the severity of AVH compared to baseline). The scoring system of the HCS allows estimation of a percentage of AVH change after rTMS treatment. A score of 5 or less ascribed by the medical evaluator at W3 indicates a decrease of 50% or more of AVH. In this case, the patient will be considered a ‘responder’. Otherwise, the patient will be considered a ‘non-responder’. The AHRS and HCS will be employed to assess the severity of AVH and the efficacy of rTMS therapy. AHRS and HCS will be recorded at each time point of this study (W0, W3, W7, and W15).

The Positive And Negative Syndrome Scale [34] is a 30-item scale, which is widely used to assess the overall disease severity of schizophrenia such as psychosis-related symptoms (hallucinatory behavior, delusions, emotional withdrawal, stereotyped thinking) and general psychopathology (including ‘poor attention’, depression and anxiety). In addition, the Psychotic Symptom Rating Scale (PSYRATS [35]), a 17-item scale, will be employed to evaluate the psychotic symptoms (hallucinations and delusions) and the Scale for the Assessment of Negative Symptoms [36], a 25-item scale, will be used to assess the negative symptoms in schizophrenia.

Comorbid depressive symptoms will be investigated with the Beck Depression Inventory [37], a 13-item, self-report rating inventory and the Calgary Depression Scale for Schizophrenia, a 9-item structured interview scale [38].

Finally, the Short Form (36) Health Survey, a 36-item scale, will be used to obtain a measure of the health-associated quality of life such as physical functioning, bodily pain, role limitations due to physical health problems, role limitations due to personal or emotional problems, emotional well-being, social functioning, energy/fatigue, and general health perceptions [39].

All of the above clinical scales will be recorded at baseline (W0) and at several stages following the end of the rTMS treatment (W3, W7, and W15). More precisely, clinical assessments at W3 will be mainly performed on Tuesday or Wednesday. It will be used to follow symptomatology of schizophrenia across this study and to investigate the impact of rTMS treatment on such symptoms, in particular AVH. Moreover, baseline AVH severity levels could also constitute a marker of the rTMS response in schizophrenia patients.

##### Neuropsychological assessments

A neuropsychological assessment evaluating performance on several cognitive domains (more specifically, executive function, mental flexibility, inhibition, verbal fluency, memory, and writing abilities) will be carried out on each participant. These data recorded at baseline (W0) will be used to evaluate cognitive impairment and identify potential neuropsychological markers associated with rTMS response. Carried out in the post rTMS period, this assessment will also allow study of the impact of multiday rTMS regime on cognitive function.

The assessment will be performed prior (W0) and, most importantly, at several intervals following the end of the rTMS regime (W3, W7, and W15). It will include the following tasks: the Trail Making Test A and B [40], the Stroop test [41], the Hanoi Tower [42], the Wisconsin Card Sorting Test [40], a Verbal Fluency task [40], the California Verbal Learning test [43], the Digit Span and Visual Memory tests [44], an autobiographical memory task [45], and a dictation writing task [46].

##### Neurophysiological assessments

Before and after rTMS treatment, cortical excitability measures will be assessed for each patient using a standard 70 mm figure-of-eight coil (MCF-B65 Butterfly Coil, MagVenture A/S, Farum, Denmark) attached to a MagPro R30 stimulator with MagOption (Medtronic A/S, Copenhagen, Denmark). The MT will be assessed using the TMS Motor Threshold Assessment Tool (MTAT 2.0, http://www.clinicalresearcher.org/software.htm). Self-adhesive, solid gel-coated disposable Ag*/*AgCl surface electrodes placed on the first dorsal interosseous hand muscle will be employed to record these measures. Peak-to-peak MEP amplitudes will be recorded at 120% of the individual MT.

Moreover, several neuroexcitability abnormalities have been described in schizophrenia patients, essentially in cortical inhibition. A deficit of intracortical inhibition (ICI) is the most robust finding in this patient population, whereas deficits of the cortical silent period (CSP) and MT have been reported inconsistently [47]. In our protocol, the CSP, ICI, and intracortical facilitation (ICF) will also be recorded to monitor potential motor intracortical changes following the rTMS treatment over the left TPJ. To this regard, a recent clinical case reported indirect signs of clinical improvement and motor excitability changes via CSP in a pontine stroke patient after rTMS treatment delivered over the left TPJ to treat their AVH [48]. The CSP will be evoked by applying TMS intensity at 120% of the individual MT while patients will perform a hand isometric contraction of approximately 50% of their maximum force. The duration of the CSP will be measured from the end of MEP until the re-occurrence of EMG activity. ICI and ICF will be determined using a paired-pulse paradigm. The conditioning subthreshold stimulus, which will be set at 80% of MT, will be preceded by a suprathreshold stimulus test at 120% of the MT. Interstimulus intervals will be set at 2 and 4 ms for ICI and at 10 and 15 ms for ICF. The EMG activity will be recorded by a computer using System PLUS EVOLUTION software (version 1.04, Micromed, Mâcon, France).

The MEPs amplitude at 120% of the MT as well as CSP, ICI, and ICF will be obtained prior (W0) and following the rTMS treatment (W3, W7 and W15) and will be used to estimate individual levels of motor cortical excitability between ‘responder’ and ‘non-responder’ patients, monitoring potential changes of such across treatment and during follow-up. Electrophysiological measures comparing pre versus post rTMS between ‘responders’ and ‘non-responders’ could constitute a potential explanatory marker informing on rTMS mechanism of action.

##### Biological measures from blood samples

Brain-derived neurotrophic factor (BDNF) is a neurotrophin that plays a key role in neuronal survival and synaptic plasticity (i.e. morphological and physiological changes of synapses induced by neuronal activity changes). BDNF levels may reflect a decrease or increase of brain activity and provide a potential explanatory marker of rTMS effects [49]. Serum BDNF levels will be measured and compared between ‘responder’ versus ‘non-responder’ patient groups and also between active rTMS versus sham rTMS stimulated groups of patients. This will allow investigation of rTMS-induced brain plasticity changes [50].

To this end, blood samples will be collected from all patients in the morning (before 10:00 a.m.) at baseline (W0) and after the end of the regime (W3, W7, and W15) in a 3.5 mL serum separator tube (SST™ II Advance, BD Vacutainer^®^, New Jersey, USA). Blood samples will be stored at room temperature for 20 min, then centrifuged at 3500 rpm at 4 °C for 20 min. Serum will be separated from blood and kept in a refrigerator at − 30 °C prior to analyses. Serum optical density will be measured at 450 nm using a microplate reader (EZ Read 400, Biochrom, Cambridge, UK). BDNF concentrations will be determined by comparing the optical density to a standard curve.

### Participant timeline

The week prior to the onset of the 10-day rTMS treatment, clinical scales, neuropsychological tests, structural and functional MRI recordings, neurophysiological motor excitability evaluations, and biological markers from blood serum samples will be obtained. Once baseline recordings are completed, the rTMS treatment will start. Each patient will receive a total of 20 sessions of 1 Hz rTMS (1200 pulses/session, two sessions/day from Monday to Friday, over two consecutive weeks), delivered on the left TPJ region. Once the rTMS treatment is completed, many of the same clinical, neuropsychological, neuroimaging, and neurophysiological measures determined during the baseline prior to rTMS regime onset will be recorded again to evaluate the impact of stimulation (Fig. 1).

### Data collection and management

A CRF will be used to collect the data for each participant. To preserve patient anonymity, an identification code is allocated during the enrollment phase allowing patient identification on the CRF. Throughout this trial, CRFs will be reviewed to ensure complete and accurate collection of data following each assessment. CRFs will be stored in a locked cupboard for data security. MRI data will be stored on a computer secured by a password and will be identified with the patient’s identification code to preserve anonymity.

### Statistical analysis

#### Sample size

The aim of this trial is to investigate the difference in brain functional and structural connectivity in schizophrenia patients receiving an active rTMS treatment and clinically responding to it or not as assessed by an amelioration of their AVH symptoms. Therefore, the sample size was calculated to determine the number of patients to be included in the active rTMS group on the basis of the primary outcome, namely the difference in FA values at baseline between ‘responders’ and ‘non-responders’. Unfortunately, no study provides a significant difference of rs-fMRI measures or FA values for a given tract (such as the left arcuate fasciculus) before and following a clinically effective versus a non-clinically effective rTMS treatment in schizophrenia patients, which would allow us to accurately estimate the adequate sample size for our trial. Nonetheless, FA values are highly reproducible and have a reliable estimation of variance. Therefore, we focused on FA values to determine sample size. Therefore, on the basis of a significant difference in the FA values between schizophrenia patients and healthy subjects for the left arcuate fasciculus [51] and assuming an α risk of 0.05 and a 1-β power of 0.80, we estimated the need to include 32 patients for the active rTMS group. To overcome an estimated 10% drop-out, we increased our recruitment needs for active rTMS group to 35 patients. Given a proportion of ‘responders’ and ‘non-responders’ to rTMS treatment as the one we propose for AVH in schizophrenia estimated at 40% and 60%, respectively [52], we will divide our cohort into 14 ‘responders’ and 21 ‘non-responder’ patients. According to a prior study [22], a minimum of 14 participants per group (‘responders’ or ‘non-responders’) has been deemed sufficient to conduct statistical analysis in neuroimaging and detect a significant effect of rTMS on brain structural connectivity. Moreover, a sham rTMS group of 10 patients will be followed in parallel to control for the placebo rTMS effect on AVH. As a result, the total number of participants required for the study is of 45 patients.

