Importantly, in our trial, we will define clinical response to active rTMS as a reduction of 50% in the HCS measured at the end of rTMS treatment (W3) compared to baseline evaluation (W0); this criteria of response is commonly found in rTMS studies in schizophrenia [27, 52, 73, 74]. Nevertheless, the response criteria may vary in some studies in which ‘responders’ are defined as patients showing a reduction of 30% in the PSYRATS [75, 76] or the AHRS scale [77]. Even though different scales such as the PSYRATS or the AHRS scales have both been shown to exhibit good psychometric reliability, the HCS seems to be the most sensitive to rTMS effects on AVH [13, 69] and thus will be applied to classify patients as ‘responders’ or ‘non-responders’ to rTMS. Using this same criterion to classify patients with positive (for ‘responders’) or negative (for ‘non-responders’) clinical responses to rTMS, our protocol predicts 40–50% success rate, thus proving beneficial for at least half of actively stimulated patients.

With regards to the neuroimaging datasets, three sequences (structural 3D-T1 MRI, functional rs-fMRI, and DWI) will be acquired prior and following the multiday rTMS protocol. MRI acquisition sessions will take approximately 30 min for each patient. Schizophrenia patients could have difficulty staying quiet and motionless for a long time in an unnatural environment such as the MRI bore. Thus, the final rs-fMRI sequence chosen, which is relatively short compared to similar studies in healthy participants, is the result of a tight compromise that aims to optimize the investigation of brain functional connectivity in this specific population.

In our trial, we will also determine the levels of BDNF in blood serum for each subject at baseline (W0) and at several stages following the end of the rTMS regime (W3, W7 and W15). BDNF plays a key role in neuronal survival, neurogenesis, the growth of dendrites and axons, synapse formation and synaptic strength gain [78]. Thus, increases of this factor may likely reflect or impact the level of brain plasticity and excitability changes induced by rTMS [49], which could potentially correlate with the magnitude of rTMS effect on AVH in schizophrenia patients. Moreover, baseline blood levels of BDNF could be predictive of clinical response.

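### The planned 14 responders and 21 non-responders are 40% and 60% of the 35 recruited; after the plan's own drop-out about 13 and 19 are expected, below the cited 14 per group

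*Protocol article*

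**What the plan says.** All references are to the protocol article.

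- **Sample size, power.** The calculation rests on a "significant difference in the FA values between schizophrenia patients and healthy subjects for the left arcuate fasciculus", "assuming an α risk of 0.05 and a 1-β power of 0.80". The result is: "we estimated the need to include 32 patients for the active rTMS group". No FA difference, standard deviation, sidedness or assumed split is printed.
- **Sample size, drop-out.** "To overcome an estimated 10% drop-out, we increased our recruitment needs for active rTMS group to 35 patients".
- **Sample size, groups.** Responder and non-responder proportions are "estimated at 40% and 60%, respectively". Applied to the 35, they give 14 and 21. The next sentence cites a prior study for "a minimum of 14 participants per group" as sufficient.
- **Exit criteria and Discussion.** Patients who do not complete the rTMS sessions are withdrawn. The Discussion adds that the data of patients who stop attending, or who miss more than two consecutive sessions, are left out of the analyses.
- **Outcome measures.** Response is classified from the Hallucinations Change Score at week 3, after treatment.
- **Discussion, response criterion.** The predicted success rate is 40–50%, "thus proving beneficial for at least half of actively stimulated patients".

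**The concern.** The three patients added to cover drop-out (35 − 32) are used twice: once as expected losses, and again as analysed members of the responder and non-responder groups. The figure of 14 responders is reached only if nobody drops out and exactly 40% respond. It is also exactly the group size that the section goes on to cite as sufficient, so there is no margin.

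The primary comparison is baseline FA between responders and non-responders, and the smaller group limits its precision. A reader of a null result would take it as a comparison of 14 v 21 with 80% power. The group sizes are too favourable on the plan's own assumptions, and the power figure was worked out for a different contrast.

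**Working it through.** **Inputs.** Required active patients 32, drop-out 10%, recruited 35, response 40% and cited group size 14 (all Sample size); upper response rate 50% (Discussion).

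**1. The plan's own figures.**
- Drop-out step: 32 × 1.1 = 35.2, which rounds to 35. Dividing instead gives 32/0.9 = 35.6, so 36. The stated 35 is reproduced to within one patient.
- Groups: 0.40 × 35 = 14 and 0.60 × 35 = 21. Both are reproduced, and both use the number before drop-out.

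**2. Groups after the planned drop-out.**
- Evaluable: 35 × 0.9 = 31.5, so 31 or 32.
- At 40%: 0.40 × 31.5 = 12.6 responders and 0.60 × 31.5 = 18.9 non-responders. With 32 evaluable: 12.8 and 19.2. Rounded, 13 v 19.
- At 50%: 0.50 × 31.5 = 15.75 per group, about 16 v 16.

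**3. Chance of at least 14 responders.** The number of responders is binomial(n, p), and the table gives P(X ≥ 14).

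| Evaluable n | p = 0.40 | p = 0.50 |
|---|---|---|
| 31 | 0.34 | 0.76 |
| 32 | 0.40 | 0.81 |
| 35 (no drop-out) | 0.56 | 0.91 |

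**4. Recruitment needed to expect 14 responders at 40%.** 14/0.40 = 35 evaluable, and 35/0.9 = 38.9, so 39 active patients.

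**5. Detectable difference.** For a two-sample t test, two-sided 0.05, 80% power, solve for d in the noncentral t distribution with n1 + n2 − 2 degrees of freedom and noncentrality d × √(n1·n2/(n1 + n2)).
- 13 v 19: d = 1.04
- 12 v 19: d = 1.07

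These are for one tract, before any adjustment over tracts.

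**6. What can be said about the 80%.** The effect size is not printed, so the 32 cannot be re-derived. It can only be bracketed by assumption:
- If 32 is a total planned as 16 v 16, the implied d is 1.02. Power is then 0.784 at 12.8 v 19.2 and 0.777 at 12.6 v 18.9.
- If the 32 already assumed a 40/60 split, the implied d is about 1.05, and power is 0.793 at 12.6 v 18.9.

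On either assumption, unequal groups and drop-out cost about 1 to 2 points.

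**The case against.** **The 14 and 21 are expectations, and 14 is only a precedent.** The sentence starts from an estimated proportion, and the prior study is cited as support after the power calculation, not as a condition for the analysis. This stands. A reader might infer that the plan guarantees 14 responders, but it does not. The expectation itself is still computed on the wrong base.

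**40% is the low end.** The Discussion gives 40–50%, and at 50% about 16 responders are expected. This also stands, and is why both rates are shown. The Sample size section nevertheless plans on 40%.

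**The drop-out allowance is adequate.** It is: 35 against 36 is a rounding matter of one patient (31.5 against 32 evaluable). The documents do not support calling the allowance materially wrong.

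**The 80% power is not refuted.** Correct. A reader might infer from the smaller groups that the trial falls well short of 80%. With no effect size or standard deviation printed, that cannot be shown; if 32 is a total, the loss is about 2 points. A large loss (power about 0.47) follows only if 32 was meant per group, whereas the text gives it for the whole active group. A loss from sharing alpha equally over tracts would also be an assumption, because the Structural connectivity analysis section plans permutation adjustment.

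**The proxy effect is disclosed.** The section says openly that no study supplies the responder contrast, and the Abstract calls the study exploratory. Using a surrogate is therefore a stated limitation and not an error. What remains is that the 80% figure should not be read as power for the responder comparison.

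**Conclusion.** The concern holds in a narrow form. The group sizes in the Sample size section take no account of the drop-out that the same section allows for. On the plan's own 10% loss and 40% response, about 13 responders and 19 non-responders are expected, not 14 and 21. The cited 14 per group is then more likely missed than met: the chance of at least 14 responders is 34–40%, and 56% even with no losses. At 50% response it is 76–81%. These figures assume independent responses and 31 or 32 evaluable patients.

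The 80% power can be neither confirmed nor refuted from the document. It was derived from a patient-versus-healthy FA difference in one tract, so it does not establish power for the responder contrast.

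One minor slip belongs with this point. The Discussion turns a predicted 40–50% into a benefit for no fewer than half of the patients, although 50% is the top of its range. It enters no calculation.

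**What to change.** 1. Keep 35 recruited. Restate the evaluable groups as about 13 responders and 19 non-responders at 40% response (about 16 v 16 at 50%), described as expected and not fixed.
2. State that the 80% power was derived from a single-tract patient-versus-healthy difference and does not establish power for the responder contrast.
3. Give the detectable standardised difference at about 13 v 19: d about 1.04–1.07 for one tract, two-sided 0.05, 80% power, before any multi-tract adjustment.
4. Report the primary FA difference with a confidence interval, so that a null result is read against its precision.
5. In the Discussion, make the statement about half of the patients agree with 40–50%.

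The cost is text only, with less favourable stated figures; the design and the planned tests do not change. If the sponsor prefers to keep 14 responders as an expectation at 40% response, about 39 active patients would have to be recruited, four more than planned.

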In this protocol, we chose to administer two sessions of 1200 pulses of 1 Hz rTMS per day (interleaved by a TMS-free 1 h interval) across two consecutive weeks, from Monday to Friday (10 days in total). The doubling of daily rTMS sessions aims to increase the total number of delivered stimuli, enhance effect magnitude and duration, and shorten stimulation regime duration. To this regard, fundamental studies evaluating changes of primary motor cortex excitability in healthy participants have shown, for example, that the higher the number of stimuli, the longer the duration of rTMS inhibitory effects [70, 71].

During the description of the study to patients, the investigators will clearly specify that rTMS therapy occurs daily over two consecutive weeks (except on weekends). After the inclusion phase, a prospective schedule for the rTMS sessions (and other appointments) will be proposed to be approved by each patient. If necessary, the appointment time can be modified and adapted to the patient requirements. If once duly informed about the schedule, a patient declares that they cannot attend all the planned rTMS sessions over 2 weeks, they will not be included in the study. In that case, an active rTMS treatment with a more flexible schedule can be offered to these patients, outside this research protocol. If the participant misses an appointment, it is possible to shift the sessions of a day. In case a patient stops attending the rTMS sessions before the end of the treatment or if they are unable to attend to more than two consecutive rTMS sessions for any reason, investigators will consider that the established research protocol is no longer respected. The participant will then be withdrawn from the study and their data will not be considered in the analyses. This situation will not suppose any change for the medical attention or treatment the patient undergoes in our institution.

Regarding potential rTMS targets in AVH, work published by Hoffman et al. [25, 72] has shown that active (but not sham) rTMS over the left TPJ induces higher levels of clinical improvement than stimulation on temporal and frontal areas. Therefore, the current protocol will employ MRI-based neuronavigation to localize the Wernicke’s area in the left TPJ according to specific spatial coordinates (MNI coordinates: x = − 69, y = − 41, z = 11) on each individual participant MRI.

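### The 14 responder / 21 non-responder split is counted on all 35 active recruits and ignores the stated 10% drop-out; among analysable patients it is about 13/19, just below the cited 14 per group

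*Protocol article*

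**What the plan says.** The Sample size section of the protocol article bases the active arm on the primary comparison, baseline fractional anisotropy (FA) in responders against non-responders. The steps are:

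- The effect is borrowed: "on the basis of a significant difference in the FA values between schizophrenia patients and healthy subjects for the left arcuate fasciculus". The error rates are "assuming an α risk of 0.05" and "a 1-β power of 0.80".
- The result is "we estimated the need to include 32 patients for the active rTMS group".
- Drop-out is then added: "To overcome an estimated 10% drop-out, we increased our recruitment needs for active rTMS group to 35 patients".
- With responders and non-responders put at 40% and 60%, the text continues "we will divide our cohort into 14" responders and 21 non-responders.
- It then reports that in an earlier study "a minimum of 14 participants per group" was considered enough for a neuroimaging analysis.

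On losses, the Exit criteria withdraw patients who cannot have the first MRI or do not complete the rTMS sessions. The Discussion adds, for a patient who stops attending or misses more than two consecutive sessions: "The participant will then be withdrawn from the study and their data will not be considered in the analyses". The Discussion also gives an expected success rate of 40-50%.

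**The concern.** The counts 14 and 21 add up to 35, which is everyone recruited to the active arm. The sentence before had raised the number from 32 to 35 because some patients would be lost, and lost patients are not analysed. The same patients therefore serve both as the allowance for drop-out and as members of the groups to be compared.

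The responder group is the smaller side of the primary comparison and limits its precision. The printed 14 also equals the per-group figure cited as sufficient, so the text reads as if that figure were reached. Once the stated drop-out is applied, the expected responder count falls below it.

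The wording adds to the problem. Response is read from the Hallucinations Change Score after treatment, so the sizes of the two groups are an outcome and cannot be set in advance.

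**Working it through.** **Inputs.** From the Sample size section: 32 needed, 10% drop-out, 35 recruited, 40%/60% response split, 14 per group. From the Discussion: withdrawn patients' data not analysed; response range 40-50%. Assumed here: each recruit drops out independently with probability 0.10, and drop-out is unrelated to response.

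**1. The plan's own figures.**
- Drop-out: 32/0.9 = 35.6 and 32 × 1.1 = 35.2. The stated 35 agrees with either to within a patient.
- Split: 0.40 × 35 = 14.0 and 0.60 × 35 = 21.0. The printed split is reproduced exactly, and only on all 35 recruits.

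**2. The split after the stated drop-out.**
- Expected completers: 0.9 × 35 = 31.5.
- On 31.5: 0.40 × 31.5 = 12.6 responders and 0.60 × 31.5 = 18.9 non-responders.
- On the 32 the calculation asks for: 12.8 and 19.2.

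Both round to 13/19. The non-responder group is comfortably above 14; the expected shortfall is in responders only.

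**3. Chance of reaching 14.** Each of the 35 recruits is an analysable responder with probability 0.9 × p, where p is the response rate. The number of responders is then Binomial(35, 0.9p). For both groups, the number of completers C is Binomial(35, 0.9), and the probability that 14 ≤ responders ≤ C − 14 is summed over C.

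| Response rate | Expected responders | P(at least 14 responders) | P(both groups at least 14) |
|---|---|---|---|
| 40% | 12.6 | 0.37 | 0.34 |
| 45% | 14.2 | 0.59 | 0.49 |
| 50% | 15.75 | 0.78 | 0.55 |

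**4. Spread of the responder count.** With exactly 32 analysed and 40% response, the 2.5% and 97.5% points of Binomial(32, 0.40) are 8 and 18.

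**5. Chance of keeping 32.** P(at least 32 of 35 complete) = P(Binomial(35, 0.9) ≥ 32) = 0.53.

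**6. Effect on power.** The protocol gives no FA difference, standard deviation or allocation behind the 32, so the 32 cannot be reproduced. Assume a two-sided two-sample t test at 0.05, with the 32 split 16 v 16. Power of 80% then implies a standardised difference of 1.02. At that difference (noncentral t), power is 0.82 at 14/21 and 0.79 at 13/19; at 12.6/18.9 it is 0.78. If the 32 had instead been calculated at a 40/60 split, 13/19 would have about 80% power by construction.

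**The case against.** The best defence is that the size rests on the FA calculation, which gave 32. The 14 is a supporting remark taken from an earlier study and is not an input to the power. The sentence about dividing the cohort starts from an estimated proportion, so it can be read as a loosely worded expectation. The study calls itself exploratory, and 45% or 50% response is within its own predicted range. All of this stands, and it limits the point to a misprinted expectation. It does not rescue the 14/21, because the 40% used to get it, applied to the patients who will be analysed, gives about 13/19.

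Drop-out may also be related to response, since worsening symptoms is one of the exit criteria. If every loss came from would-be non-responders, 14 responders could remain among 31.5 (14/31.5 = 44%). The protocol does not say this.

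A reader might infer more than the text supports:

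- **That the 32 analysable patients will probably be missed.** They are slightly more likely to be reached than not (0.53). The gap between 35 and 36 is rounding.
- **That 14 per group is possible only with no drop-out.** At 40% response it is the expected count that reaches 14 only with no drop-out. The actual count can still reach 14 by chance, or through a higher rate: 14 of 32 is 43.75%, inside the stated range.
- **That the design fails to deliver its 80% power.** At the expected split the loss is one to two percentage points, under an effect the protocol does not state.
- **That the sham arm has the same fault.** It has no stated target for analysable patients or power, so losing one of its 10 contradicts nothing.

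**Conclusion.** The printed split is wrong as written. It counts all 35 recruits one sentence after allowing for losses, and the protocol excludes withdrawn patients from the analyses. The expected split among analysable patients is about 13/19, so the responder group is expected to fall about one patient short of the 14 cited as sufficient.

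At 40% response, the rate used for the split, 14 in both groups is more likely missed than met (met with probability 0.34). At 45% it is about even (0.49), and at 50% slightly more likely met than missed (0.55). These figures assume 10% drop-out that is independent between patients and unrelated to response.

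The consequence is a misstatement of the group sizes for the primary comparison. It is not a material loss of power and does not call the trial's size into question.

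**What to change.** In the Sample size section:

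1. Replace the 14/21 split with the expected split among analysable patients: 35 recruited, 31 to 32 analysable after 10% drop-out, about 13 responders and 19 non-responders at 40% response.
2. State that responder numbers are an outcome of the trial, with a 95% range of about 8 to 18 among 32 at 40% response, and reword the phrase about dividing the cohort to match.
3. Next to the cited 14 per group, say that 14 responders is not assured and that at 40% response it is more likely missed than met.
4. If power is restated, say that the loss at 13/19 is small (about 78-79%, if the 32 assumed 16 v 16) and name that assumption.

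The cost is the wording of one paragraph and slightly less favourable printed figures. No extra patients are needed, and nothing in the conduct of the trial changes.
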